### Interventions and Anticipated Theory of Change

The program’s theory of change is shown in Figure 1, with inputs and interventions leading to short-term outputs, which in turn lead to medium-term outcomes, and finally long-term impacts. The HRP condition–specific, algorithm-driven, color-coded protocols tailored for 3 cadres of HWs serve as readily accessible reference documents for managing HRP cases. Since these protocols have been vetted and formally endorsed by the UP health department, and since ARMMAN is implementing the program in partnership with health departments of 2 intervention districts, we anticipate cooperation from district health systems throughout the 18 months of the implementation period. This cooperation is expected to include nomination of ANMs, MOs, and specialists for training and other supportive supervision initiatives. Classroom training on HRP protocols is designed to refresh and strengthen HW’s knowledge and skills to manage HRPs. It is expected to provide them with around 10% immediate gain in theoretical knowledge and skills to manage or refer HRPs (based on evidence from phase-1 protocols in Telangana, which showed 8%‐17% gain in knowledge among ANMs) [30]. Training supplemented with digital interventions provides HWs, particularly ANMs, with real-time responses to queries they get during management or referral of HRP cases in actual field conditions. These processes translate knowledge into practice, resulting in early diagnosis and appropriate management or referral of the HRP cases according to type of health facility (short-term output).

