#### Hypothesis and Outcomes

The program’s impact evaluation will test the following research hypotheses: (1) Does the program, implemented over 18 months, enhance knowledge, skills, and confidence of the ANMs and the MOs to make early diagnosis and manage the 3 HRPs in the intervention arm, compared to usual care arm? (2) Can the capacitated ANMs and MOs translate their knowledge and skills into practice, particularly for early diagnosis and end-to-end management of the 3 HRP conditions in the intervention arm, compared to the control arm? (3) Does the program improve the quality of ANC services in the intervention arm, compared to the usual care arm?

At the system level, the primary outcomes focus on changes in the knowledge and skills of HWs. The first outcome is the net change in correct knowledge and skills of ANMs to manage (treat, counsel, refer, and follow-up) women with any of the 3 HRP conditions (anemia, PIH, and APH) from baseline to end line, comparing intervention and control arms. The second outcome is the net change in correct knowledge and skills of MOs to manage (treat, counsel, refer, and follow-up) women with any of the 3 HRP conditions (anemia, PIH, and APH) from baseline to end line, comparing intervention and control arms. The percentage of correct knowledge and skills for ANMs and MOs will be calculated based on the number of correct responses provided out of a total of 45 questions on the 3 HRPs, administered at baseline and end line surveys.

The system-level secondary outcomes include the net change in the ability of ANMs to correctly identify HRP-related signs and symptoms from baseline to end line, in intervention versus control arm and net change in the ability of MOs to do the same. Other outcomes include changes in the confidence level of ANMs and MOs to manage HRPs between baseline and end line across 2 arms and to document qualitatively whether any systematic barriers reported by district officials at baseline survey were overcome by the end line, by comparing intervention and control arms.

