### Study Tools

Baseline and end line surveys will use qualitative methods for collecting data from the system stakeholders and quantitative methods for collecting data from the community, specifically the RDW. The data collection tools were pretested in Telangana in 2022-2023 and subsequently adapted to align with the programs and policies of UP. Table 2 provides details of respondents interviewed using qualitative data collection technique.

**Table 2. T2:** Respondents, data collection method, sample size, and information areas of qualitative data collection tools.

Type of respondent and tool	Data collection method	Sample size	Who collects data?	Recruitment strategy	Key information areas of tool
Chief medical officer (Multimedia Appendix 1)	In-depth interview	1 per district	Qualitative researchers	Purposive	District policies and programs on maternal and newborn health Facilitators and barriers to implement IHRPTM^a^ program in district
Associate chief medical officer (Multimedia Appendix 2)	Semistructured interview	1 per district	Qualitative researchers	Purposive	Most prevalent HRPs^b^ in district Vulnerable areas or populations Issues with collection of RCH^c^, HMIS^d^, or HRP data Human resources availability
Specialist gynecologists (district hospital; Multimedia Appendix 3)	In-depth interview	1 per district	Qualitative researchers	Purposive	ANC^e^ case load at facility HRP case load at facility Volume of high-risk cases referred to facility Volume of late and unnecessary referrals Strategies for coping with referrals
Medical officers working in PHC^f^ and CHC^g^ (Multimedia Appendix 4)	Semistructured interview	4‐5 per district	Qualitative researchers	From 4 randomly selected PHCs of 2 blocks in a district	Support systems available for ensuring quality ANC Case load of ANC and HRPs Knowledge about 3 specific HRPs Management skills to care for women with 3 HRPs Knowledge about referral practices to woman with 3 HRPs
ANMs^h^ working in HSCs^i^ (Multimedia Appendix 5)	Semistructured interview	8‐10 per district	Qualitative researchers	2 ANMs per PHC, from above 4 randomly selected PHCs of 2 blocks in a district	Support systems available for ensuring quality ANC Case load of ANC and HRPs Knowledge about 3 specific HRPs Management skills to care woman with 3 HRPs Knowledge about referral practices to woman with 3 HRPs

a IHRPTM: Integrated High-Risk Pregnancy Tracking and Management.

b HRP: high-risk pregnancy.

c RCH: reproductive and child health.

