### Ethical Considerations

#### Overview

Qualitative data at baseline and end line surveys will be collected by ARMMAN researchers using computer-assisted personal interview (CAPI) tools, while quantitative data will be outsourced to a professional data collection agency, with prior experience in collecting maternal and child health–related data in UP. At baseline, a 2-day meeting of the qualitative researchers was held to discuss specific nuances of each question of the qualitative tool, how to ensure uniformity while asking questions, distribution of qualitative data collection workload, etc. For the baseline RDW tool, the investigators and supervisors of the shortlisted agency were trained for 5 days by ARMMAN program’s research team on the following topics: IHRPTM program and its objectives, ethical practices to be adhered to while collecting data from RDW, how to and when to approach potential gatekeepers, which RDW are eligible for consent or assent, how to obtain consent or assent, how to collect data using CAPI technique; importance of privacy during data collection, confidentiality of data, data quality, and potential risks and mitigation measures. Baseline RDW data were collected by female investigators or supervisors using the CAPI tool. All the tools were translated into Hindi and back translated into English, to ensure accuracy and retain the meaning of questions and most of the questions in the background, ANC, and delivery care sections were tried and tested in other large-scale surveys like NFHS.

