## Discussion

### Overview

One of the major strengths of this study is that this study is being implemented in partnership with state and district health departments. Through our multicomponent interventions, the capacity of public health care system stakeholders (ANMs, MOs, and specialists) is being built to diagnose and manage HRP conditions at their respective facilities. If ANMs and MOs manage HRPs at their level, there will be a reduction in unnecessary or late referrals to tertiary or higher-level facilities, allowing these facilities to concentrate mainly on the most critical cases. The study will establish a robust system for not only managing HRPs but for ensuring quality ANC services and continuum of care in geographies with poor maternal outcomes (Table 1). If the program is successful in these areas, it will pave the way for future implementation efforts in other states.

The proposed study anticipates a few limitations, such as delays in getting permissions to collect data from ANM, MOs, specialists, and RDW from the 2 control districts. In intervention districts, many MOs have recently joined the service, and their focus is on preparing for higher studies. Therefore, they may not be very keen to participate in this program. Also, if they get admission in higher studies, they will leave the service, and refilling the position may take time. We are also concerned about the support for the program from system stakeholders who are nearing retirement and working on a contractual basis. The end line qualitative results, particularly from the 2 intervention districts, might be influenced by social desirability bias, as by then, the majority of the system stakeholders will be aware of the purpose of the program and its objectives. To minimize the social desirability bias, we will do data collection methods triangulation and information triangulation (collecting same data from multiple question formats). To minimize the bias, we will also triangulate both qualitative and quantitative data, wherever feasible. Frequent transfers of district and state officials may also create hurdles in the timely implementation of interventions and getting approvals for implementing interventions on the ground.

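### The implementer's own researchers, who know the arm, collect both system-level primaries, and the only safeguard described targets respondents, so interviewer or scorer expectation at end line could pass into the DiD

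*Protocol article*

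**What the plan says.** **System level.** Under Ethical Considerations, Overview: "Qualitative data at baseline and end line surveys will be collected by ARMMAN researchers using computer-assisted personal interview (CAPI) tools". The same body runs the program; under Interventions and Anticipated Theory of Change the article says that "ARMMAN is implementing the program in partnership with health departments of 2 intervention districts". Table 2 gives the ANM and MO tool as a semistructured interview, with 8-10 ANMs and 4-5 MOs per district. The two system-level primaries are percentages of correct knowledge and skills, from the "number of correct responses provided out of a total of 45 questions on the 3 HRPs, administered at baseline and end line surveys" (Hypothesis and Outcomes). No scorer is named.

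**Community level.** Data from recently delivered women (RDW) are collected by an outsourced professional agency. For the baseline RDW tool its investigators and supervisors were "trained for 5 days by ARMMAN program’s research team on the following topics: IHRPTM program and its objectives", among other topics. The primary is the proportion of women with one of the three conditions whose problem resolved before delivery and who reported satisfaction with its management. The sample size section says that the condition data rest on self-report.

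**Allocation and safeguard.** The program covers whole districts, so the district identifies the arm. The Discussion recognises respondents' social desirability bias in the end line qualitative results and answers it this way: "To minimize the social desirability bias, we will do data collection methods triangulation", together with asking for the same information in several formats and comparing the two data sources.

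**The concern.** The program's own staff gather the data for two primary outcomes in a format that leaves room for probing and judgement. They know which districts received 18 months of their work. The safeguard is directed at what respondents may choose to say. It does not address what an interviewer may prompt, or what a scorer may accept.

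DiD removes bias that is equal in both arms within a round, or constant over rounds within an arm. It does not remove an expectation that the intervention districts should by now have improved, because that expectation exists in one arm at one round. It would probably favour the program, and the evaluation is meant to inform scale-up to 75 districts. Comparing two data sources does not remove the bias if both may carry it.

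**Working it through.** The article gives no figure for this bias, so there is none to reproduce. The check sets out what the arrangements imply and then illustrates the scale.

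**1. Who knows what**
- ANM and MO interviewers: implementer staff at both rounds, with allocation by district. Arm, round and aim are known to them.
- RDW interviewers: briefed on the program and its aims at baseline. Knowledge of the arm is not stated. Survey Design has the respondent lists checked against the local ANM's list, so the arm could be guessed at end line, but that is an inference.
- Scorer of the 45 items: not stated.

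**2. How bias enters the estimate**

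DiD = (I1 − I0) − (C1 − C0), where I and C are the intervention and control means, 0 is baseline and 1 is end line.
- Bias b in I1 only: DiD shifts by b.
- Bias b in I1 and C1: shift b − b = 0.
- Bias b in I0 and I1: shift b − b = 0.

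The baseline briefing, given to interviewers for both arms, therefore does no harm by itself. Harm needs knowledge or a guess of the arm, and a change between rounds.

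**3. Scale of one item**

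1/45 = 2.2 percentage points; 2/45 = 4.4 points. The article expects a gain of around 10% straight after classroom training. Read as percentage points, that is 0.10 × 45 = 4.5 items, so two items would be 4.4/10 = 44% of it. That gain is an immediate one and not the 18-month net effect, so the ratio shows scale only.

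**4. False-positive rate if there is no true effect**

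Rate = P(|Z + b/SE| > 1.96). Bias sizes, SDs and proportions are assumed; no design effect is applied.

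Scores: SE = SD × √(4/n), SD 10-15 points, two districts per arm.
- ANMs, n = 2 × 8 to 2 × 10 = 16-20 per arm and round: SE from 10 × √(4/20) = 4.47 to 15 × √(4/16) = 7.5 points. One item: about 6%-8%. Two items: about 9%-17%.
- MOs, n = 8-10: SE 6.32 to 10.61 points. One item: about 5.5%-6.4%. Two items: about 7%-11%.

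Community primary: SE = √(4p(1 − p)/n). The expected case counts give n from 400 + 120 + 100 = 620 to 500 + 200 + 340 = 1040 per arm and round, ignoring overlap; p = 0.3-0.5.
- SE from √(4 × 0.3 × 0.7/1040) = 2.8 to √(4 × 0.5 × 0.5/620) = 4.0 points.
- Bias of 2 points: about 8%-11%. Bias of 5 points: about 24%-42%.

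All are to be read against 5%. Clustering would widen the SEs, and an analysis that allowed for it would show less inflation. The shift in the estimate itself would not change.

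**The case against.** The strongest reply is that the evidence for the community outcome is thin. The training sentence concerns the baseline tool only, the agency is external, and nothing says that its staff were told which districts have the program. This stands. A reader might infer that both sets of primaries are collected by people who know the arm; for the women's survey the article does not support that.

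Second, no scorer is named and the ANM and MO tools sit in appendices that are not shown. If the 45 items are closed and keyed in the electronic tool, lenient marking has little room. A reader might infer that the interviewers themselves judge which answers are correct; the article does not say so. The possibility of prompting in a semistructured interview remains.

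Third, some partial safeguards exist: a two-day meeting of the qualitative researchers that covered uniform questioning, repeated question formats, a photograph of the antenatal card, the mother's own account, and a satisfaction rating that is the woman's own answer. These may reduce interviewer variation, but none hides the arm.

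Fourth, silence on masking in a condensed article is weak evidence. That is right. The point rests on the staffing and training that the article does state.

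**Conclusion.** The concern holds in limited form. It is documented that implementer researchers who know arm and round collect the data for both system-level primaries. It is also documented that RDW interviewers were briefed on the program's aims at baseline, and that the described safeguard is directed at respondents. It follows by arithmetic that expectation bias confined to the intervention arm at end line passes one for one into the DiD.

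Its size is unknown. The 2.2 points per item is exact, but the number of items affected, any misrecording among women, and the false-positive rates above depend on assumed values. A reader might also infer that masking at end line would be almost free and complete. The article says nothing on its feasibility or cost, and interviewers facing trained ANMs and MOs cannot readily be masked. This is a worthwhile, low-cost improvement to the end line and not a defect that invalidates the design.

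**What to change.** For the end line:

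1. **Agency interviewers.** Do not repeat the training module on the program and its aims, and do not disclose which districts are intervention districts. Keep the consent information truthful. Where practical, let each team work in both districts of a matched pair (Shravasti with Gonda, less than 50 km apart; Sambhal with Budaun, less than 100 km apart). State in the plan what interviewers will be told.
2. **ANM and MO scores.** Strip district, arm and round from the recorded answers. Have existing researchers score the 45 items against a fixed key, with baseline and end line answers in one pool, as far as item-level baseline answers were kept. The numeric codes described under Confidentiality replace names when results are presented; they would have to be extended to hide these labels from scorers.
3. **Limitation.** State that the face-to-face ANM and MO interviewers cannot be masked, so masked scoring removes lenient marking but not prompting.

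Cost: revised training material, a de-identification step, scoring time for existing staff and some travel between paired districts. Masking will be imperfect, because women may mention the program and a trained worker's answers may reveal the training. Intervention, sample and estimator are unchanged.

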#### Privacy

While collecting qualitative or quantitative data from the field, there will be situations when interviews cannot be conducted in complete privacy, as participants may be surrounded by other adult members or coworkers. During the training of data collection teams, the issue of privacy was discussed in detail, specifically focusing on two subtopics: (1) ways to minimize situations where the investigator is surrounded by other adults (starting the interview with generic issues like crops, yield, etc, till other adults move and the supervisor tries to move other adults to a separate location, etc) and (2) strategies (such as preinterview briefings about privacy, choosing alternate locations, and scheduling flexible times when fewer people are around) that can be adopted during data collection to move other people away from the interview site.

#### Confidentiality

During data collection, the respondent’s name will not be recorded whenever possible. In cases where names are collected during qualitative interviews, these will be converted into numeric codes (eg, ANM-1 and ANM-2) while presenting the results. At the time of in-depth interviews (IDIs) with district officials, although we record the name of the respondent on the hard copy of the tool, this is done solely to ensure we are interviewing the correct person. Identification details of these respondents will be anonymized once the transcription and translation of the IDIs are complete. IDIs were not audio recorded and were conducted in the presence of a notetaker. Identification details of IDIs were anonymized once the notes were converted into digital data.

During baseline, after completing the RDW interview, the interviewer saved and closed the file before leaving the interview site. Each interviewer was provided a password for sharing and uploading the completed files through email. A unique ID was assigned to each RDW to protect their identity. The uploaded datasets were downloaded centrally at the ARMMAN Hyderabad office on a password-protected computer. All electronic data were stored securely on a password-protected computer at ARMMAN until the completion of the end line survey. Access to identifiable information is restricted only to the research team. The data files, containing identifiers, will be stored separately from other data files and will be password-protected, with access restricted to the research team. To ensure confidentiality and secure data transfer or sharing, files containing identification details will be password-protected and encrypted. All hard copy records will be destroyed at the end of the project.

#### Data Storage and Sharing Policy

In accordance with the principles of transparency and reproducibility, all deidentified datasets (both qualitative and quantitative) will be securely stored on password-protected servers at ARMMAN for a minimum of 5 years following project completion. Thereafter, data will either be archived for secondary use or permanently destroyed. Only deidentified, aggregate-level data may be shared upon reasonable request from accredited researchers or institutions, contingent on prior approval from ARMMAN’s scientific review board and Sigma’s institutional review board (IRB), and in compliance with national data protection regulations.

#### Approvals

The study got approvals from ARMMAN’s scientific review board (017/2024) and Sigma, New Delhi’s IRB (10009/IRB/24‐25).

### Data Analysis

The qualitative data will be analyzed using Braun and Clarke’s [44] inductive thematic analysis framework. Interviews with system stakeholders (eg, chief MOs, associate chief MOs, MOs, and ANMs) conducted in Hindi and transcribed verbatim will be translated into English and back-translated to ensure both linguistic and conceptual accuracy. The 2 researchers will independently code the transcripts using ATLAS.ti (ATLAS.ti Scientific Software Development GmbH) or NVivo (Lumivero) software. The analysis will follow a structured process: (1) initial data familiarization, (2) development and iterative refinement of an inductive coding framework, (3) systematic application of codes, (4) and identification of emergent codes where necessary. Themes will be generated through synthesis and organization of the coded data. Anticipated themes include training and handholding of ANMs and MOs on HRPs, motivation and job satisfaction of ANMs and MOs, quality ANC, facilitators and barriers to HRP management, facility and community support to ANMs and MOs, workforce shortages, sociocultural barriers to ANC and HRP care, and demand for services. Interrater reliability will be ensured by having 2 researchers independently code 20% of the transcripts. Any discrepancies will be resolved through consensus. Thematic findings will be validated against existing literature and substantiated with verbatim participant quotations. This rigorous, transparent, and software-supported approach will ensure analytical robustness of the findings.

Using data validation checks, the quality of the quantitative data will be assessed for coverage, consistency, and completeness by ARMMAN researchers. The analysis of these data will be done using SPSS (version 21.0; IBM) or STATA (version 12.0; Stata Corp, LLC) software. Preliminary analysis includes frequency tables and cross-tabulations, while as part of advanced analysis, multivariate analysis techniques will be used. The cleaned data will be analyzed according to background characteristics; coverage and quality of the ANC, delivery, postnatal care; the outcome and output indicators; satisfaction with the care; etc. Advanced analysis will be carried out to quantify associations of the background characteristics with output and outcome indicators. As far as possible, quantitative results will be reported with effect estimates, 95% CIs, and significance levels.

We will use the DiD technique to estimate the causal effect of program interventions on outputs (eg, RDW sensitized and HRPs diagnosed early) and outcomes (eg, protocol-based management and referral of HRPs). This approach compares changes in outputs and outcomes over the intervention period (18 months) between the intervention and the usual care arms. For each quantitative output and outcome indicator summary, descriptive DiD or net change will provide causal effect of intervention on the indicator. The DiD-specific regression models will then be used to test whether interventions were significantly associated with changes in the outcomes and to assess the extent of changes relative to the control group.

To address the issue of missing data in the RDW dataset, before applying DiD, we will assess the extent and patterns of missingness—whether missing data are at baseline, end line, or both—and examine whether missingness is random or systematically related to intervention status or outcomes by comparing covariates and outcomes between complete and missing cases. Given the robust data quality assurance measures implemented during both surveys, we anticipate minimal missingness, and any missing data are expected to be missing at random. If the proportion of missing at random for any outcome or covariate exceeds 10%, we will apply appropriate imputation methods prior to fitting the DiD model. The DiD model will then include intervention and control status, baseline and end line survey indicators, and interaction terms between outcomes and covariates.

During the granular analysis of testing the association between background characteristics and output and outcome indicators, we will draw upon the WHO’s Social Determinants of Health framework [45]. Intersectionality between the background and confounding variables will be explored using subgroup analysis. In the multivariate regression model, predictor variables will only be included after testing for multicollinearity using variance inflation factor to ensure stability and reliability of the model.

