## Methods

### Study Design

The study adopts a “matched, before-after quasi-experimental design with a control (usual care) arm,” as a randomized control study design is not feasible for this kind of system and community-based implementation study. Both qualitative and quantitative data will be collected at the system and community levels, respectively, during baseline (prior to implementation of interventions) and end line (after 18 months of interventions)*,* in the intervention and control arms. The program’s effectiveness at the system level will be evaluated by assessing the capacity of ANMs and MOs to diagnose and manage the 3 HRPs and at the community level by measuring the proportion of RDW with any of the HRP conditions, whose HRP problem got resolved prior to delivery and who were satisfied with the care they have received for the HRP condition*.* Effectiveness of the program through quantitative indicators will be analyzed using the difference-in-difference (DiD) technique.

However, keeping in view the quasi-experimental design of this study, to control for potential baseline differences between intervention and control arms due to nonrandom allocation, we will lock the analysis plan by prespecifying primary outcomes and covariates of the quantitative data. Prior to advanced analyses, we will implement near-matching of intervention and control data on key covariates, such as age, parity, caste, and literacy. In addition, during the main analysis stage, we will apply DiD models with covariate adjustment to further control for any residual imbalance and to strengthen causal inference.

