Given the low prevalence of PIH and APH (around 5%), with 1% margin of error, our study (2000 RDW per arm) is adequately powered at 95% (a conservative estimate). With a higher margin of error (say 1.5%), although the required sample size per arm will reduce to 821, the power of the study will fall below 95%, and the anticipated number of RDW with PIH and APH would be too small to compare (approximately 70‐130 per arm). This would result in high CIs, making HRP-specific impact evaluation a challenging task.

As different respondents will be surveyed at baseline and end line, there is no risk of data attrition. However, since HRP conditions data in this study is relying on self-reports by RDW and expected low prevalence of PIH and APH conditions (around 5%) in India, nonparticipation by RDW with these conditions could compromise the statistical power of the study. To overcome this problem, we have set a narrow margin of error (1%, ie, prevalence could range between 4%‐6%) for baseline and end line estimates in each arm. Our sample size calculation also accounts for a 10% nonresponse rate per arm at both baseline and end line. To increase the effective prevalence of the APH condition, the inclusion criteria for this condition encompass APH, placenta previa, and abruptio placenta. With recent estimates in India showing an increase in prevalence of PIH to 11% [43], while moderate or severe anemia was stagnant at around 26% [39], we are confident of including sufficient RDW with these 2 conditions. Nevertheless, if the prevalence of any of the 3 HRPs falls below 4% at baseline or end line in either arm, the statistical power of the study for that HRP condition will be compromised. We acknowledge this as a limitation of the study.

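### The sentence listing the DiD regression terms names the wrong interaction: it omits arm-by-survey, the term that carries the programme effect

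*Protocol article*

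**What the plan says.** All places are in the Methods of the protocol article.

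- **Target (Data Analysis).** "This approach compares changes in outputs and outcomes over the intervention period (18 months) between the intervention and the usual care arms". This is the usual DiD contrast, and it is stated correctly.
- **Descriptive estimate (Data Analysis).** "For each quantitative output and outcome indicator summary, descriptive DiD or net change will provide causal effect of intervention on the indicator".
- **Task of the regression (Data Analysis).** "The DiD-specific regression models will then be used to test whether interventions were significantly associated with changes in the outcomes", and to size those changes relative to the control group.
- **Terms of the regression (Data Analysis, end of the paragraph on missing data in the survey of recently delivered women).** "The DiD model will then include intervention and control status, baseline and end line survey indicators, and interaction terms between outcomes and covariates". No other sentence lists model terms.
- **Role of covariates (Study Design).** "we will apply DiD models with covariate adjustment to further control for any residual imbalance and to strengthen causal inference". The stated reason is "to control for potential baseline differences between intervention and control arms due to nonrandom allocation".
- **Sampling (Sample Size of the Quantitative Surveys).** "As different respondents will be surveyed at baseline and end line, there is no risk of data attrition". The data are therefore two cross-sections per arm, not a panel.

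**The concern.** The regression is asked to test whether the change from baseline to end line differs between arms. A model with arm and survey as main effects forces that change to be the same in both arms. Only an arm-by-survey product lets it differ, and the coefficient of that product is the DiD. Because different women are interviewed at the two surveys, there are no within-woman change scores that could carry the contrast instead.

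The interaction that is named, between outcomes and covariates, is not a usable regressor. The outcome is the dependent variable, so a product containing it is a function of the model's own error term.

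What is at stake is the adjusted estimate, its confidence interval and its significance test. Study Design relies on covariate adjustment and on a locked analysis plan to protect a nonrandomised comparison. If the published model stands, a correct analysis departs from it, and a literal one does not answer the question.

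**Working it through.** The article gives no figure on this point, so there is nothing to reproduce. The check asks which listed coefficient, if any, equals the DiD.

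**Inputs.** The listed terms, the target and the repeated cross-sections come from the sections cited above. The cell proportions (30% to 60%) and the 500 women per cell are assumptions for illustration.

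**1. Notation.** Let a be the control proportion at baseline, s the change in control, g the baseline gap (intervention minus control) and d the DiD. The four cell means are:
- control baseline: a
- control end line: a + s
- intervention baseline: a + g
- intervention end line: a + g + s + d

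**2. Main effects only, equal cells.** The arm coefficient is the average of the two within-survey arm differences:

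(g + (g + d)) / 2 = g + d/2

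Likewise, the survey coefficient is (s + (s + d)) / 2 = s + d/2. Two coefficients cannot separate the three unknowns g, s and d. With unequal cells the arm coefficient is g + w·d for some weight w between 0 and 1, so the conclusion is the same.

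**3. Numbers.** Least squares on the four cell means:

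| Case | Control base / end | Intervention base / end | True d | g + d/2 | Arm coefficient, no product | Arm-by-survey coefficient, if included |
|---|---|---|---|---|---|---|
| A | 0.40 / 0.45 | 0.40 / 0.60 | 0.15 | 0 + 0.075 | 0.075 | 0.15 |
| B | 0.40 / 0.45 | 0.50 / 0.55 | 0 | 0.10 + 0 | 0.10 | 0 |
| C | 0.40 / 0.45 | 0.30 / 0.50 | 0.15 | -0.10 + 0.075 | -0.025 | 0.15 |

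The arm coefficient is half the effect in A, purely the baseline gap in B, and of the wrong sign in C.

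**4. Simulation.** Settings: 300 replicates, linear probability model, robust errors, independent women, and one covariate distributed alike in all four cells. Mean coefficients:

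| Case | Arm: arm + survey + covariate | Arm: same, plus outcome × covariate | Arm-by-survey, when included |
|---|---|---|---|
| A | 0.074 | 0.074 | 0.147 |
| B | 0.101 | 0.101 | -0.006 |
| C | -0.026 | -0.026 | 0.148 |

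Adding the outcome-by-covariate product, as the sentence literally asks, does not restore the effect. Adding arm-by-survey does. In case B, where the programme does nothing, the arm coefficient is significant at 5% in 99.7% of replicates. That rate ignores clustering by sampling unit, which affects the standard errors but not which term identifies the effect.

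**5. Is a baseline gap plausible here?** Table 1 gives the share with at least 4 antenatal visits: 42.3% (Shravasti) and 32.9% (Sambhal), against 41.7% (Gonda) and 40.6% (Budaun). Weighting districts equally, as the design of 1000 women per district does:
- intervention: (42.3 + 32.9) / 2 = 37.6
- control: (41.7 + 40.6) / 2 = 41.15
- g = 37.6 - 41.15 = -3.55 points

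With that gap, a true DiD of 2 × 3.55 = 7.1 points would give an arm coefficient of zero. These are 2019-2021 district figures for one component of the antenatal-package outcome. They show only that gaps of a few points are realistic.

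**The case against.** The strongest reply is that the intent is plain. The same section defines the target correctly, calls the regression a DiD model and says that it measures change relative to control. Such a model contains an arm-by-survey contrast by definition, and a competent analyst would include it. A full specification may also sit in a locked plan that is not shown.

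Most of this stands as a statement about intent, and the sentence is probably a drafting slip. It does not rescue the text. An article may leave model terms to an analysis plan, but this one lists them and gives the wrong interaction, and Study Design adds only covariate adjustment.

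Some stronger readings are tempting but unsupported:

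- **That the study cannot estimate the programme effect.** The descriptive net change, "descriptive DiD or net change will provide causal effect of intervention on the indicator", still gives an unadjusted point estimate. The defect is confined to the regression.
- **That the arm coefficient will be reported as the effect.** No passage says so. The figures above show that no listed term is the DiD; they do not predict a bias in the published result.
- **That the sentence governs every outcome.** It closes a paragraph on the survey of recently delivered women. It is not clearly the model for the health-worker knowledge outcomes.
- **That the effect scale is also wrong.** No logistic model is named, and not every outcome is a proportion; one is a mean gestational month. Nor need an adjusted DiD equal the unadjusted one.
- **That district-pair or urban/rural terms are required.** This is a separate modelling preference and does not bear on the missing interaction.

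**Conclusion.** The concern holds for the regression as written. The only sentence listing its terms leaves out arm-by-survey and puts the outcome on the right-hand side, so no listed coefficient is the DiD that the section sets out to test. With equal cells the arm coefficient is g + d/2: half the effect when there is no baseline gap, and the gap alone when there is no effect. The algebra does not depend on the assumed proportions; the numerical examples do. The adjusted estimate, its interval and its test are affected, and the unadjusted descriptive net change is not. This is a wrongly stated analysis rule, most likely a drafting error, and it should be corrected before the end line analysis that the article schedules for March-June 2026.

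**What to change.** Replace the sentence with: *The DiD model will include arm, survey (end line vs baseline), the arm x survey interaction, whose coefficient is the programme effect, and the prespecified covariates.*

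Delete the reference to interactions between outcomes and covariates. If covariate-by-arm or covariate-by-survey terms were meant, name them and say why they are included.

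The cost is one sentence in the protocol, carried into the locked analysis plan. No data collection, sample size or outcome definition changes.
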